## Methods / Design

This study has two parts: Study 1) A cross-sectional study to identify and characterize balance control strategies after mTBI compared to healthy controls, and Study 2) An interventional randomized pilot study using a novel ABF rehabilitation technique to improve central sensorimotor integration after mTBI. All subjects will complete baseline clinical sensory, ocular motor, vestibular, neurocognitive, static and dynamic balance, and central sensorimotor integration testing. Following baseline testing, a subset of mTBI participants will be randomized into two treatment groups for 6 weeks of rehabilitation. Within 1 week after completing the rehabilitation program, subjects will repeat the balance and central sensorimotor integration testing to examine the short-term effects of rehabilitation. Subjects will complete the balance and central sensorimotor integration testing a third time, 6 weeks after completion of the rehabilitation, to assess retention. This trial is registered at clinicaltrials.gov (NCT02748109).

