#### Intervention

Participants will be randomized into either 1) a standard of care vestibular rehabilitation program or 2) a standard or care vestibular rehabilitation plus ABF training program. Rehabilitation will begin approximately 7-10 days after pretest assessment. Both groups will receive the rehabilitation that includes progressive (3 levels of difficulty) exercises that target gaze stabilization, vestibular stimulation, balance and proprioceptive retraining [50–52] (Table 5). Subjects randomized to the ABF training, will undergo the same vestibular rehabilitation program but will wear an ABF device while performing the rehabilitation exercises. All researchers performing post-rehabilitation testing will remain blinded to the randomized group assignment throughout the duration of the study.

**Table 5 Tab5:** Rehabilitation protocol

Exercise	Vision	Surface	Time	Progression	ABF
Static Balance	Eyes open	Firm	30 s per condition	10 double stance conditions including tossing a ball, head rotations left-right, head rotations up-down, head rotations with smooth pursuit, with gaze stabilization, and with saccades	Pitch modulated feedback for AP sway, direction modulated for ML sway
	Eyes closed	Firm	30 s per condition	3 double stance conditions including head rotations left-right, head rotations up-down	
	Eyes open	Foam	30 s per condition	4 double stance conditions including tossing a ball, head rotations left-right, head rotations up-down	
	Eyes closed	Foam	30 s per condition	3 double stance conditions including head rotations left-right, head rotations up-down	
Dynamic Balance (Tandem Gait)	Eyes open	Firm	30 s per condition	4 tandem gait conditions including tossing a ball, head rotations left-right, head rotations up-down	Direction modulated for ML sway
	Eyes closed	Firm	30 s per condition	1 tandem gait condition	
	Eyes open	Foam	30 s per condition	4 tandem gait conditions including tossing a ball, head rotations left-right, head rotations up-down	
	Eyes closed	Foam	30 s per condition	1 tandem gait condition	
Dynamic Balance (Bending down)	Eyes open	Firm	30 s per condition	3 different heights	Direction modulated for ML sway
	Eyes closed	Firm	30 s per condition	3 different heights	
Dynamic Balance (Squatting)	Eyes open	Firm	30 s per condition	4 squats including sit-to-stand, lunge, lunge onto unstable surface, and lunge + twist	Direction modulated for ML sway

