#### Statistical analysis

To determine if ABF intervention improves central sensorimotor integration, we will build linear regression models to simultaneously evaluate the change in CSMI measures reflecting central sensorimotor integration and the effect of ABF compared to standard of care. Our outcome will be the change in pre- versus post-rehabilitation program CSMI measures; using the change (difference) in CSMI measures will control for the correlation of the repeated pre- and post- measures within an individual as well as maximizing the number of covariates we can potentially add into the regression models. Covariates of interest are vestibular/ocular motor scores, PTSD, Veteran versus civilian status, age, and gender. In addition, we will determine whether rehabilitation improved the static and dynamic balance metrics that were measured at the pre- and post-rehabilitation testing visits.

To determine if people with CSMI impairment show sustained improvement in static and dynamic balance after rehabilitation, even after ABF is discontinued, we will use linear mixed effects regression modeling which will include a third time point of interest (6 weeks after the rehabilitation intervention has stopped). Time will be treated as a categorical variable in order to evaluate changes in CSMI scores and balance during specific time periods, in this case, between the cessation of the intervention and the 6 weeks post-intervention follow-up. We will explicitly test the significance of a group by time interaction to determine if participants in the ABF rehabilitation group showed sustained improvements in outcomes beyond that experienced by participants with the standard of care. If applicable, we will then stratify the analysis by those with abnormal/normal measures of vestibular/ocular motor function to assess the relationship between vestibular/ocular motor function deficits and sustained improvement in CSMI score and balance.

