If a portion of subjects with chronic balance problems after mTBI have abnormal CSMI test measures but normal clinical vestibular testing results, this suggests that sensory integration processes in the brain can be impaired following mTBI, even without peripheral sensory deficits, and that abnormal central sensorimotor integration plays a key role in persistent abnormal balance in subjects with normal vestibular function. If a portion of mTBI subjects have abnormal CSMI test measures and abnormal clinical vestibular function, the key mediator for balance problems is less clear and may be due to the peripheral vestibular dysfunction, abnormal central sensorimotor integration, or inadequate adaptation of central sensorimotor integration to account for abnormal sensory information. If we find that abnormal central sensorimotor integration mediates abnormal static or dynamic balance, rehabilitation will need to be focused on improving central sensorimotor integration to improve balance. If we find that CSMI scores improve with rehabilitation, we will conclude that central sensorimotor integration strategies are flexible and can improve with training. Further, if we find that central sensorimotor integration and gait and balance jointly improve with rehabilitation, we will have further evidence that central sensorimotor integration plays a key role in the mediation of gait and balance following mTBI. If we find a greater improvement in the ABF group, we will conclude that ABF may facilitate improved rehabilitation. Finally, if we find that people with central sensorimotor integration impairment maintain improvements after stopping the use of ABF device, we will conclude that a recalibration of sensory integration and/or sensorimotor transformation for balance has occurred, rather than sensory substitution that requires active ABF. If we find that sensory strategies can change with practice and biofeedback, we will conclude that this targeted approach to balance rehabilitation should be explored further in a larger, randomized trial. It is possible that different subclasses based on CSMI measures respond differently to rehabilitation or ABF-augmented rehabilitation. In such a case, the results of this study will provide valuable information for powering an in-depth future study carefully examining the relationship between CSMI subclasses and the response to rehabilitation with and without ABF. The results of this study will further our understanding of the mechanisms underlying posture and gait dysfunction in individuals with chronic mTBI and inform future studies about the efficacy of ABF augmented rehabilitation programs.

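### The rule for concluding recalibration rests on maintained improvement after ABF stops, which shows retention only and requires no gain over standard of care

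*Protocol article*

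**What the plan says.** **The rule (Discussion).** If people with impaired central sensorimotor integration "maintain improvements after stopping the use of ABF device, we will conclude that a recalibration of sensory integration" (or of the sensorimotor transformation) has occurred, "rather than sensory substitution that requires active ABF". The sentence names no comparison with standard of care. A greater improvement in the ABF arm is dealt with in the sentence before it, and leads to a different conclusion, that ABF may help rehabilitation.

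**The analysis (Study 2, Statistical analysis).** For sustained improvement once ABF has been discontinued, a mixed model adds the third time point. The interval singled out is "between the cessation of the intervention and the 6 weeks post-intervention follow-up". The same section plans a between-arm regression of earlier change, "Our outcome will be the change in pre- versus post-rehabilitation program CSMI measures", and a group-by-time test of sustained benefit over standard of care.

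**When ABF is used (Study 2, Intervention).** Both arms follow the same vestibular programme. Participants in the ABF arm "will wear an ABF device while performing the rehabilitation exercises".

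**When testing takes place.** Methods / Design: "Within 1 week after completing the rehabilitation program, subjects will repeat the balance and central sensorimotor integration testing", and "a third time, 6 weeks after completion of the rehabilitation, to assess retention". Study 2, Assessment procedures, words both timings slightly differently, but there too the post-test follows the end of the programme. On testers, Intervention says: "All researchers performing post-rehabilitation testing will remain blinded to the randomized group assignment".

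**The concern.** The Discussion sets two mechanisms against each other: a lasting change in how the nervous system uses sensory input, and substitution that works only while the device supplies sound. To tell them apart, an observation has to have different expected values under the two. Stability from post-test to 6 weeks does not, if the device is already off at the post-test.

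The rule also needs no advantage over the control arm. Three sources could give the ABF arm a lasting improvement that owes nothing to ABF:

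- the exercises, which both arms do;
- practice from repeating the tests;
- regression to the mean, because Study 2 takes participants with abnormal CSMI results (Participants), defined as more than 2 standard deviations from the control mean (Study 1, Statistical analysis).

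At stake is the mechanistic conclusion of Study 2. It could be drawn from a gain unrelated to ABF, or withheld when an ABF-specific gain was seen without the device but later faded.

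**Working it through.** The plan gives no figure to reproduce here, so the check compares what each mechanism predicts at each visit.

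**Step 1: device status at each test.** ABF is described only as worn during exercises. The post-test comes after the programme ends. Its testers are blinded, which is hard to square with a participant wearing headphones and a lumbar-mounted phone. None of the tests in Tables 1 and 3 mentions ABF. Together these imply that the device is off at pre-test, post-test and 6 weeks. The article does not say so outright.

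**Step 2: expected values.** Let *g* be the gain common to both arms (exercises, retesting, regression to the mean) and *r* the extra gain in the ABF arm that is expressed without the device. At a later visit the expected change from baseline is *g* + *r* with ABF and *g* with standard of care, so the difference is *r*. Substitution that needs the active device means *r* = 0 at every device-off visit.

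**Step 3: illustration.** Assumed, not from the article: *g* = 0.3 SD, held to 6 weeks; *r* = 0.5 SD where recalibration occurs. Entries are in SD.

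| Mechanism | ABF arm: pre, post, 6 wk | Standard arm: pre, post, 6 wk | Difference, pre to post | Difference, post to 6 wk | Difference, pre to 6 wk |
|---|---|---|---|---|---|
| Substitution needing active ABF | 0, 0.3, 0.3 | 0, 0.3, 0.3 | 0 | 0 | 0 |
| Recalibration, retained | 0, 0.8, 0.8 | 0, 0.3, 0.3 | 0.5 | 0 | 0.5 |
| Recalibration, fading | 0, 0.8, 0.3 | 0, 0.3, 0.3 | 0.5 | -0.5 | 0 |

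**Step 4: reading the table.**

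- The post-to-6-week difference is 0.5 - 0.5 = 0 under retained recalibration and 0 - 0 = 0 under substitution. This holds for any size of *r*, so the assumed values do not drive it. The change within the ABF arm is also 0 in both: 0.8 - 0.8 and 0.3 - 0.3.
- Under substitution the ABF arm still keeps 0.3 SD over baseline at 6 weeks. That is a maintained improvement after stopping the device, so the rule as worded would conclude recalibration.
- Under fading recalibration the ABF advantage falls by 0.5 SD and is gone at 6 weeks. The rule would withhold its conclusion, although 0.5 SD was shown at the post-test with the device off.
- The pre-to-post difference is 0 under substitution and 0.5 SD under either form of recalibration. The pre-to-6-week difference separates substitution from retained recalibration. Both come from device-off tests already planned.

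**The case against.** The strongest reply is that the Discussion sentence names neither a visit nor the post-to-6-week contrast. An improvement is measured from baseline, so a maintained improvement at two device-off visits is itself device-off evidence, which is the right kind. The control arm does the same exercises and stops at the same time, and the group-by-time test compares the arms. The remark is also only one interpretive sentence in a study that calls itself a pilot.

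Part of this stands. The trial collects what is needed, and the planned between-arm contrasts from baseline can address the question. What does not stand is that the rule uses them. The Discussion does not tie recalibration to a difference from standard of care, and hypothesis (c) of the second goal (end of Background) has no comparator either. A gain from baseline within the ABF arm still contains the common component.

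A reader might infer more than the article supports:

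- *That fading gains would be read as substitution.* The rule runs in one direction. Failure to maintain would only withhold the recalibration conclusion, and other sentences in the Discussion would still credit improvement in CSMI scores and a greater gain with ABF.
- *That a test with the device on is needed.* It is not. Substitution that requires active ABF predicts no ABF-specific gain with the device off, and device-off testing can contradict that.
- *That the design cannot separate the mechanisms.* The contrasts from baseline can; the post-to-6-week change cannot.

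**Conclusion.** The interpretation rule is wrong as written; severity is minor to moderate. Change from post-test to 6 weeks has the same expectation, 0, under active-device substitution and under retained recalibration, so it speaks to retention only. Because the rule requires no gain beyond standard of care, a lasting gain shared by both arms would satisfy it: 0.3 SD in the illustration, and any positive value in principle.

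This rests on one inference, that testing is done without ABF at every visit. It follows from the timing, the blinding and the silence of Tables 1 and 3, but is not stated. The SD values are assumptions used to show the pattern; the equality of the post-to-6-week contrast does not depend on them. The design, visits, models and sample size are not faulted by this point.

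**What to change.** Reword the interpretation in the Discussion, and align the sustained-improvement paragraph of the Study 2 Statistical analysis with it:

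1. Base the conclusion against substitution that needs active ABF on the device-off ABF-minus-standard difference in change from baseline to post-test, and from baseline to 6 weeks. The first comes from the planned change-score regression. The second comes from the planned mixed model with categorical time and a group-by-time term.
2. Treat change from post-test to 6 weeks as retention after training ends, and do not use it to distinguish the two mechanisms.
3. Do not draw the recalibration conclusion from maintenance within the ABF arm alone.

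A short statement that all tests are done without ABF in both arms would help the reader, but that is procedural detail the full protocol may already hold.

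The cost is wording only, with no new visit, test or participant. The downside is that the retention visit, and any maintenance seen within one arm, then support a narrower claim.

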
## Abbreviations

ABF: Auditory biofeedback
ANAM: Automated neuropsychological assessment metrics
AP: Anteroposterior
AUC: Area under the receiver-operator characteristic curve
BDI-II: Becks depression inventory
BESS: Balance error scoring system
CoM: Center of mass
CSMI test: Central sensorimotor integration test
CTSIB: Clinical test of sensory organization and balance
CV: Coefficient of variation
DHI: Dizziness handicap inventory
FRF: Frequency response function
LOC: Loss of consciousness
ML: Mediolateral
mTBI: Mild traumatic brain injury
NSI: Neurobehavioral symptom inventory
PLI: Pain location inventory
PTSD: Post-Traumatic stress disorder
RMS: Root-mean-square
SCAT3: Sport concussion assessment Tool 3
SF-36: Short form 36
SOT: Sensory organization Test
TBI: Traumatic brain injury.
